## Abstract

Background: There is a lack of psychometric evidence about pediatric health-related quality of life (HRQoL) instruments. Evidence on cost effectiveness, involving the measurement of HRQoL, is used in many countries to make decisions about pharmaceuticals, technologies, and health services for children. Additionally, valid instruments are required to facilitate accurate outcome measurement and clinical decision making. A pediatric multi instrument comparison (P-MIC) study is planned to compare the psychometric performance and measurement characteristics of pediatric HRQoL instruments. Methods: The planned P-MIC study will collect data on approximately 6100 Australian children and adolescents aged 2–18 years via The Royal Children’s Hospital Melbourne and online survey panels. Participants will complete an initial survey, involving the concurrent collection of a range of pediatric HRQoL instruments, followed by a shorter survey 2–8 weeks later, involving the collection of a subset of instruments from the initial survey. Children aged ≥7 years will be asked to self-report HRQoL. Psychometric performance will be assessed at the instrument, domain, and item level. Conclusions: This paper describes the methodology of the planned P-MIC study, including benefits, limitations, and likely challenges. Evidence from this study will guide the choice of HRQoL measures used in clinical trials, economic evaluation, and other applications.

## 1. Introduction

The increasing recognition of the importance of including the child’s perspective on their health and wellbeing in decision making has resulted in a large increase in the availability and use of pediatric health-related quality of life (HRQoL) instruments [1,2]. Accurate measurement and valuation of HRQoL among children plays a vital role in the development of robust evidence for economic evaluation and population health studies, as well as routine outcomes measurement, clinical decision making and patient choice [1,3].

Economic evaluation frequently incorporates preference-based HRQoL information to produce estimates of Quality Adjusted Life Years (QALYs). QALYs combine HRQoL impacts and survival impacts in a single metric, allowing comparisons across health problems, interventions, and populations. QALYs are based on patients’ HRQoL which is usually captured with validated survey instruments. These instruments comprise a descriptive system covering different HRQoL aspects, which is weighted and scored using QALY weights (or utility values) derived from the stated preferences, usually of the general population for each health state. QALYs inform cost-effectiveness evidence which is formally used in many countries to make decisions about public funding for pharmaceuticals, technologies, and health services. In Australia, bodies such as the Pharmaceutical Benefits Advisory Committee (PBAC) and Medical Services Advisory Committee (MSAC) use evidence about cost effectiveness to inform decisions about the best use of health care resources [4]. These decisions have large cost implications, with approximately $12.6 and $25 billion spent through the Pharmaceutical Benefits Scheme (PBS) and Medicare Benefits Schedule (MBS), respectively, in Australia in 2019–2020 [5,6]. These are federally funded reimbursement schemes ensuring low or no cost to consumers, and similar reimbursement processes are seen around the world.

There is increasing interest in the use of HRQoL information for patient reported outcome measures (PROMs) in clinical practice. In the clinical setting, HRQoL instruments can be used to aid identification of health problems, including unexpected or hidden problems; decision making, including prioritization of health problems or treatments; monitoring of changes in health over time; communication; and patient decision making, including decision making about treatments [7]. PROMs information has been shown to improve HRQoL outcomes and satisfaction with pediatric clinical care [3,8,9]. In this context it is important that the HRQoL instrument is sensitive to change, informative to clinicians and patients, consistent with a patient’s clinical history and allowing for a short collection time. However, there is a paucity of literature on the psychometric properties, feasibility and validity of potential PROM instruments. A 2015 systematic review identified 35 generic paediatric PROMs with none having all their psychometric properties assessed [9]. Eight of the 35 measures identified were preference-based measures [9].

Although there are established methods for measuring and valuing HRQoL in adults [10], considerable challenges arise in applying these methods to children, in particular very young children [11]. For instance, the developmental range of children precludes a ‘one size fits all’ approach and younger children are unable to self-report their HRQoL, requiring proxy completion (usually by parents) [11].

A 2015 systematic review examining the application of preference-based HRQoL instruments in pediatric populations identified nine HRQoL instruments that have been used in pediatric populations (Adolescent Health Utility Measure, Assessment of Quality of Life (AQoL-6D), Child Health Utility (CHU9D), EQ-5D-Y-3L, Health Utilities Index Mark 2 (HUI2) and Mark 3 (HUI3), 16D, 17D, and the Quality of Wellbeing Scale (QWB)) and concluded that more evidence on the performance of these instruments is required [12]. Additionally, a 2021 systematic review examining the psychometric performance of key generic pediatric preference-based instruments (CHU9D, EQ-5D-Y-3L, HUI2, and HUI3) also identified gaps in evidence on the psychometric performance of pediatric HRQoL instruments. Key limitations in the currently available literature include the small sample size of some studies, wide variation in methods, a focus on single instruments, limited coverage and heterogeneity of disease conditions or age groups, meaning that broad synthesis of evidence is challenging [13]. These limitations have resulted in ambiguity regarding which pediatric HRQoL instruments are most appropriate for which context, inhibiting clinicians in instrument use for clinical care, researchers in evidence collection and decision makers in evidence appraisal. No study has previously compared a wide set of generic HRQoL measures accompanied by preference weights concurrently in the same cohort of children (also called a pediatric multi instrument comparison (P-MIC) study).

There is a clear evidence deficit regarding the comparative performance of pediatric HRQoL instruments. Considering the large implications on resource allocation and clinical care, addressing this evidence deficit provides the opportunity to improve value for money across the health care system, resulting in improved population health outcomes for children. This study aims to generate new evidence on the comparative performance of available pediatric HRQoL instruments. This will be done by assessing the validity and reliability of instruments across a range of age and disease groups in a single study. This evidence will improve and inform users’ choice of pediatric HRQoL instruments in Australia and around the world. This paper aims to describe the study methodology of the proposed study.

## 2. Materials and Methods

### 2.1. Study Aims

To compare the performance of a range of pediatric HRQoL instruments in terms of validity, reliability, responsiveness, acceptability, feasibility, and consistency across age and disease groups.

### 2.2. Study Design

This P-MIC study will involve the prospective collection of multiple generic and disease-specific paediatric HRQoL instruments concurrently via two online surveys. The first is a 15–30-min survey, and the second is a five-minute follow-up survey two to eight weeks later. Collecting these paediatric HRQoL instruments concurrently across a range of age and disease groups will allow the relative performance and measurement characteristics of these instruments in children to be assessed. This study was approved by The Royal Children’s Hospital (RCH) Human Research Ethics Committee (HREC/71872/RCHM-2021) on the 20th May 2021 and is prospectively registered with the Australia New Zealand Clinical Trials Registry (ANZCTR) (ACTRN12621000657820).

### 2.3. Timeline

Recruitment for this study began on the 4th of June 2021 and is expected to be completed by January 2022. Data analysis and publication is expected to be ongoing, with main results completed by December 2022.

### 2.4. Participants

Any parent, caregiver, or guardian of a child(ren) aged 2–18 years (inclusive) at study enrolment is eligible to take part. Participants unable to communicate in written English, unable to answer or comprehend the questions or who do not reside in Australia will be excluded from participating. Additional eligibility criteria apply to the disease-specific samples (see Section 2.6.1 for further details).

The study aims to collect data on 6100 Australian children via the recruitment of parents/caregivers. The sample will be split into three groups:Sample one, recruited via hospital: 1000 parents/caregivers will be recruited via The RCH, Melbourne, Australia, allowing data to be collected from children with a wide range of health conditions and severities.Sample two, online panel population sample: 1500 parents/caregivers of children from a general population sample will be recruited via an online survey company, Pureprofile Australia, allowing data to be collected from a large population sample. This sample will be further divided into two groups:○Sample 2a, online panel population sample, normal follow-up: 1300 parent/caregivers will be followed-up in line with the rest of the cohort, two to eight weeks after initial survey.○Sample 2b, online panel population sample, short follow-up: to assess reliability, 200 parents/caregiver will be followed up at a shorter interval, two days after initial survey.Sample three, online panel disease-specific groups sample: 3600 parents/caregivers of children with one of nine health conditions will be recruited via an online survey company, Pureprofile Australia. Disease groups were chosen that had sufficient prevalence to allow for recruitment of groups and with a focus on conditions with larger expected HRQoL decrements [14]. Currently six of the disease groups have been confirmed and include: attention-deficit/hyperactivity Disorder (ADHD), anxiety and/or depression, autism spectrum disorder (ASD), asthma, dental decay, and sleep problems. An additional three disease groups will be selected from the following: diabetes, epilepsy, eating disorder, recurrent abdominal pain, frequent headaches. We aim to collect data on 400 unique children from each of the nine disease groups.

### 2.5. Recruitment

#### 2.5.1. Sample One, Sample Recruited via Hospital (*n* = 1000)

Research Assistants (RAs) will approach parents/caregivers for recruitment from a range of RCH departments, including outpatient clinic waiting rooms, surgical department waiting rooms and the Emergency Department Short Stay Unit (SSU) and provide them with a link to the initial survey. The SSU will provide a list of approved families for RAs to approach on the day when recruiting from this department to ensure appropriate families are approached and to minimize the disruption to care and avoidable distress. Poster adverts with QR codes to the initial survey will be placed in high traffic areas of the hospital. Online advertisements with a link to the initial survey will be placed on hospital telehealth appointments (this advert will appear for any family attending a hospital appointment via telehealth), newsletters, and social media. Recruitment resources will also be utilised to target hospital departments where children likely to be experiencing higher decrements in quality of life, such as children with rare genetic conditions, children with serious sequalae arising across childhood following birth at an extremely low birthweight, and children admitted to the Paediatric Intensive Care Unit (PICU). Potential participants from PICU will be approached by PICU research staff at their pre-operative clinic visit to minimize the recruitment in inappropriate situations (e.g., where the child is unlikely to survive) and to minimize stress to families of children with an unplanned admission. If needed, we may also extend to other areas of the hospital or recruit via other methods such as sharing the advertisement with parent/caregivers from the onsite RCH childcare centre; with participants from a previous study who have indicated they would like to be contacted for future research; sending letters to potential participants from participating hospital departments; and approaching families in the local RCH playground.

#### 2.5.2. Sample Two (Online Panel Population Sample, *n* = 1500) and Sample Three (Online Panel Disease Groups Sample, *n* = 3600)

The recruitment of the online panels will be managed by Pureprofile Australia. All existing members have completed a double opt-in process to join the panel and have agreed to complete online surveys over the course of their membership. They are provided with the opportunity to accept an offer to participate in new surveys. Participants will be randomly selected from this panel to take part in this study if they meet eligibility criteria and fulfil the health status/disease-specific quotas that have been prespecified. Participants will be selected based on quotas for age and sex. As children may have multiple conditions, participants for sample three will be invited to take part on a least fill basis, whereby, children with rarer conditions will be invited to take part for the rarer condition disease group where they will only receive the disease specific measure for this condition even if they report their child has another of the disease specific conditions.

### 2.6. Data Collection

Data will be collected via two online REDCap surveys. Table 1 provides a schedule of which instruments will be collected at which time points for each sample. Appendix A provides a justification for and description of instruments included in the study.

#### 2.6.1. Initial Survey

At the start of the initial survey, parents/caregivers will be asked screening question(s) to confirm their eligibility. Parents/caregivers from every sample will be first asked to confirm they are the parent, caregiver or guardian of a child aged 2–18 years. Parents/caregivers from sample three, the online panel disease groups, will undergo additional screening to ensure they are the parent/caregiver of a child with one of the nine health conditions (Appendix B). Currently six of the nine disease groups and the corresponding screening questions for these groups have been confirmed. Once the additional three disease groups have been confirmed, the corresponding screening questions will be selected for these groups. Following screening, all participants will be required to provide informed consent. The initial survey includes sociodemographic questions, the Strengths and Difficulties Questionnaire (SDQ), EQ Health and Wellbeing Short Version for parents (EQ-HWB-S) followed by several pediatric HRQoL instruments. HRQoL instruments will be blocked into three groups: core, additional and disease-specific. Participants will be randomized to additional instruments to minimize responder burden. Core instruments, which all participants will receive, include: the Global Health Measure, CHU9D, Paediatric Quality of Life Inventory (PedsQL) Core 4.0, EQ-5D-Y, and Toddler and Infant Questionnaire (TANDI). Participants in all samples, where the child is aged five years or older, will receive both the EQ-5D-Y 3L and 5L original version. Participants in sample one, where the child is four years or younger, will receive both the EQ-5D-Y 3L and 5L adapted versions with guidance notes. Participants from samples two and three, where the child is four years or younger, will be randomized to receive either (1) the EQ-5D-Y-3L adapted version with guidance notes and original version or (2) the EQ-5D-Y-5L adapted version with guidance notes and original version. Additionally, participants from samples two and three, the online panel samples, will be randomized to receive one of three additional block(s) of instruments: (1) EQ-5D-5L & HUI2/3, (2) AQol-6D or, (3) Patient-Reported Outcome Measurement Information System 25 (PROMIS-25) Paediatric Profile. Participants from sample three, the online disease group sample, will receive a corresponding disease-specific HRQoL instrument. Currently six of the nine disease groups have been confirmed and the corresponding disease specific instruments for these groups are: PedsQL asthma model (asthma), KIDSCREEEN-27 (ASD), Sleep Disturbance Scale for Children (SDSC) (sleep problems), Child Perceptions Questionnaire (CPQ 11-14) (dental decay), The revised Children’s Anxiety and Depression Scale Short form (RCADS-25) (anxiety and/or depression), and Strengths and Weaknesses of ADHD Symptoms and Normal Behavior Scale (SWAN) (ADHD). Once the additional three disease groups have been confirmed, the corresponding disease specific measure will be selected for these groups. Disease-specific instruments are selected based on the following hierarchical criteria: (1) instrument validated in children, (2) disease-specific QoL instrument, (3) symptom scale or measure, (4) generic QoL instrument commonly used in, or appropriate for use in, children with the condition of interest. Appendix A provides the rationale for choosing each disease specific instrument.

Children aged seven years or older and identified by their parent/caregiver as being able to complete the survey will be invited to complete the HRQoL questions (self-report). If the child is under seven years of age or is unable to complete the survey (e.g., not cognitively able to complete or is undergoing a procedure in hospital) the parent/caregiver will be asked to complete the HRQoL questions on their behalf as proxy. Participants will be given HRQoL instruments to complete that match the child’s age, person reporting (proxy report vs. self-report) and child disease group (if part of the online disease panel) (see Figure 1).

The order in which the HRQoL instruments are presented for completion will be randomized to minimize order and survey fatigue effects. In addition, the EQ-5D-Y-3L, EQ-5D-Y-5L, and, if relevant the EQ-5D-5L, will be presented to participants with another HRQoL instrument separating them, given their similarities. For participants in samples two and three, where the child is four years or younger and is receiving both the EQ-5D-Y (3L or 5L) original and adapted version, the original version will be displayed directly before the adapted version. The order of instruments will be the same for the initial and follow-up survey for each participant. The consent and sociodemographic questions will always appear first in the initial survey.

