#### 2.9.1. Validity

Validity is defined as the degree to which the HRQoL instrument measures the construct(s) it purports to measure [18]. Validity will be measured using within-scale analysis (measured using factor analysis), known group differences (measured by descriptively comparing a priori assumptions regarding expected differences between groups), convergent validity (measured by analyzing the correlation of similar constructs from different instruments) and discriminant validity (measured by analyzing whether dimension responses are independent of known groups) [18,19].

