**Core HRQoL instruments**						
PedsQL	X	X	X	X	X	X
TANDI (if <=3 years)	X	X	X	X	X	X
EQ-5D-Y 3L & 5L original (if >=5 years)	X	X	X	X	X	X
EQ-5D-Y 3L & 5L adapted (if <=4 years)	X	X				
EQ-5D-Y 3L original and adapted or EQ-5D-Y 5L original and adapted (if <=4 years)			X *	X *	X *	X *
CHU9D	X	X	X	X	X	X
Global Health Measure (single item)	X	X	X	X	X	X

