## Appendix A. Overview of Instruments

**Table A1 children-08-00714-t0A1:** Overview of instruments with justification for inclusion in study.

Instrument	Description	Application in This Study	Justification for Inclusion in P-MIC
Core non-HRQoL Instruments			
EQ-HWB-S v1.2	Part of the EuroQol family of instruments, the EQ-HWB-S is a new experimental instrument designed to assess the impact of being a care recipient or caregiver on health and wellbeing [20]. The short version currently has 9 items.	See Figure 1 and Table 1.	Included following advice from consumer advisory group who felt it was important to include a carer. QoL measure due to the strong relationship between child and carer. QoL in children who have chronic conditions. The EQ-HWB-S was chosen because it is a promising new instrument that requires further validation work and is an opportunity to add to the evidence base.
SDQ	The SDQ is a well-validated behavioral screening questionnaire used to assess a child’s emotional and behavioral wellbeing [21,22]. It has 25 items measuring 5 domains [23]. Cut points on each domain can be used to indicate borderline or clinically elevated symptoms. Versions of the SDQ exist for children aged 2–17 years, with self-report available for children aged 11–17 years.	See Figure 1 and Table 1.	Included to capture emotional wellbeing of children to allow the exploration of how HRQoL instruments perform for children with a mental health problem or mental health comorbidity. The SDQ was chosen because it is well validated across a wide age range with cut points to indicate clinically relevant symptoms.
Core HRQoL Instruments			
PedsQL Generic Core 4.0	The PedsQL Generic Core 4.0 is a 23 item HRQoL instrument covering 4 domains [24]. Validated version of the PedsQL exist for children aged 2–18 years with self-report available for children ≥8 years [24].	See Figure 1 and Table 1.	Identified as priority for inclusion as it is a generic instrument widely used in pediatric populations with some evidence for performance, but requiring more.
TANDI v2	The TANDI is a new proxy HRQoL instrument developed specifically for children ≤3 years based on the structure of the EQ-5D-Y-3L [25]. It consists of 6 items covering 6 domains [25].	See Figure 1 and Table 1.	Identified as priority for inclusion because it is a promising new instrument for young children requiring further validation work.

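### The rule that separates look-alike EQ-5D forms omits TANDI, so the TANDI with EQ-5D-Y correlation is open to carry-over and should also be reported for children who saw the two apart

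*Protocol article*

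**What the plan says.** Section 2.6.1 sets the order of presentation: "The order in which the HRQoL instruments are presented for completion will be randomized to minimize order and survey fatigue effects". It then adds a constraint for forms that resemble each other: "the EQ-5D-Y-3L, EQ-5D-Y-5L, and, if relevant the EQ-5D-5L, will be presented to participants with another HRQoL instrument separating them, given their similarities". For panel children aged four or younger, one exception is stated: the original EQ-5D-Y version comes directly before the adapted one. Each participant keeps the same order at follow-up.

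TANDI is outside the constraint. Appendix A (Table A1) says: "The TANDI is a new proxy HRQoL instrument developed specifically for children ≤3 years based on the structure of the EQ-5D-Y-3L". The core set is "the Global Health Measure, CHU9D, Paediatric Quality of Life Inventory (PedsQL) Core 4.0, EQ-5D-Y, and Toddler and Infant Questionnaire (TANDI"), and Table 1 gives TANDI in all three samples at both surveys, limited by age: "TANDI (if <=3 years"). Hospital children aged four or younger "will receive both the EQ-5D-Y 3L and 5L adapted versions with guidance notes". Panel children of that age are randomised to either the 3L or the 5L, in its original and adapted versions.

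Section 2.9.1 defines convergent validity as "measured by analyzing the correlation of similar constructs from different instruments".

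**The concern.** The authors judged that random order alone is not enough for forms that look alike, and so imposed a gap between them. By the description in Table A1, TANDI is built like the EQ-5D-Y-3L, yet the gap does not apply to it. As worded, TANDI may even be the instrument that separates the 3L from the 5L.

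Randomising order balances shifts in mean score, because each form comes first about equally often. It does not protect a correlation. If a parent carries an answer from one form to a similarly built neighbour, the two scores move closer together whichever came first. The statistic at stake is the correlation between TANDI and EQ-5D-Y, which is central evidence for a new instrument that Table A1 includes because it needs further validation. Because the order is repeated at follow-up, so is any adjacency.

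**Working it through.** The article states no adjacency figure, so there is none to reproduce. The counts assume that all orders meeting the stated rule are equally likely.

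**Hospital, age 3 or under, five forms** (TANDI, 3L, 5L, PedsQL, CHU9D; global item not shuffled)
- All orders: 5! = 120. With 3L and 5L adjacent: 2 × 4! = 48. Permitted: 120 − 48 = 72.
- TANDI next to the 3L: 48, less the 2 × 3! = 12 orders in which the 5L also touches the 3L, leaves 36. So 36/72 = 50%, and the same for the 5L.
- TANDI between 3L and 5L, touching both: 2 × 3! = 12, so 12/72 = 17%.
- TANDI next to at least one: 36 + 36 − 12 = 60, so 60/72 = 83%.
- TANDI next to PedsQL: 48 − 2 × 2 × 3! = 24, so 24/72 = 33%, and the same for CHU9D.

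**Hospital, six forms** (global item also shuffled; the article does not say whether it is)
- Permitted: 720 − 240 = 480.
- Next to a given form: (240 − 48)/480 = 192/480 = 40%. Touching both: 48/480 = 10%. At least one: (192 + 192 − 48)/480 = 336/480 = 70%.
- Next to PedsQL: (240 − 96)/480 = 30%.

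With no separation rule, TANDI would touch at least one EQ-5D-Y form in 84/120 = 70% (five forms) or 432/720 = 60% (six forms). The rule therefore raises this adjacency somewhat.

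**Panel** (original and adapted versions move as one block)
- With k units, the chance that TANDI is next to the block is 2/k: 50% for four units, 40% for five, 33% for six. It is the same 2/k for PedsQL and for CHU9D.
- TANDI directly touches a given version only from one side of the block: 1/k, that is 25% for four units and 20% for five.

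**Number of children**
- Ages 2 to 18 inclusive are 17 year-groups, and ages 2 and 3 are two of them. If ages were evenly spread (an assumption): 2/17 × 6,100 ≈ 718, made up of 2/17 × 1,000 ≈ 118 hospital and 2/17 × 5,100 = 600 panel.
- Global item not shuffled: next to some EQ-5D-Y form, 118 × 0.83 + 600 × 0.50 ≈ 98 + 300 = 398; apart, about 320 (20 hospital, 300 panel).
- Global item shuffled: about 82 + 240 = 322 adjacent.

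**Possible effect on the correlation**
The documents give no carry-over size. As an illustration, let adjacency turn a share s of residual variance into shared variance. The pooled correlation is then r + q × s × (1 − r), where q is the adjacency to the form being correlated. Take r = 0.60 and s = 0.10 to 0.30, both assumed.
- Hospital, q = 0.50: 0.60 + 0.50 × 0.10 × 0.40 = 0.62, up to 0.60 + 0.50 × 0.30 × 0.40 = 0.66.
- Panel, q = 0.25: 0.60 + 0.25 × 0.10 × 0.40 = 0.61, up to 0.60 + 0.25 × 0.30 × 0.40 = 0.63.

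**The case against.** The case against has four parts.

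- **TANDI may not be similar enough to need the rule.** The three forms covered each have 5 items in 5 domains. TANDI has 6 items in 6 domains and was written for very young children. Its items are not in the article, and sharing a structure does not mean sharing wording. This stands as far as it goes: the article does not contradict itself, and how similar is too similar is a judgement. It does not show that carry-over is absent, and the stated reason for the rule, similarity, plausibly reaches TANDI.
- **A reader might infer that adjacency inflates only the correlation with EQ-5D-Y, leaving PedsQL and CHU9D as clean comparators.** The documents do not support that. Order is random across all instruments, and in the panel TANDI is next to PedsQL or CHU9D exactly as often as to the EQ-5D-Y block. In hospital the gap is 50% for a given EQ-5D-Y form against 33% for PedsQL or CHU9D. A differential bias would therefore rest mainly on carry-over being stronger between similarly built forms, which is plausible but undocumented.
- **A reader might apply the 83% to the correlation, or count all 718 children as affected.** Neither is right. A correlation is taken with one form, so 50% is the relevant hospital figure. The 718 are all the children who receive both instruments, of whom about 398 would see them side by side.
- **Random order already yields a comparison group, and analyses by order normally belong in an analysis plan, which is not shown.** The first half is true and makes the remedy cheap. The second means that the missing analysis is not itself a fault. The point concerns the scope of the rule in Section 2.6.1.

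**Conclusion.** The point holds as a minor design weakness. The separation rule omits an instrument that the article itself describes as modelled on one of the separated forms, and the TANDI with EQ-5D-Y correlation is open to carry-over that random order does not remove. The adjacency figures rest on equally likely permitted orders and, for each range, on whether the global item is shuffled and how many other forms are shown.

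The likely distortion is modest: about 0.02 to 0.06 in hospital and 0.01 to 0.03 in the panel for a given form, on a true 0.60. The carry-over share behind those figures is assumed. Indirect carry-over through the sister EQ-5D-Y form is not modelled. The counts of children assume even ages, whereas Section 2.5.2 mentions age quotas without giving them and several disease groups may contain few children this young. The documents do not show that the correlation will be biased, only that the design leaves room for it.

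**What to change.** Report the TANDI with EQ-5D-Y correlations for children whose randomised order kept the two apart, beside the full set, and base the convergent-validity conclusion on both. This needs the recorded order and one extra analysis.

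The cost is precision. Taking the standard error of a correlation of 0.60 as roughly (1 − 0.60²)/√(n − 1), it is 0.64/√717 ≈ 0.024 for 718 children and 0.64/√319 ≈ 0.036 for 320. Single-form results will be less precise, because each panel child sees only the 3L or the 5L. In hospital only about 20 children (118 × 17%) would see TANDI apart from both forms. There the split is better made form by form, with about 59 of 118 apart from a given form. Similar results in the two sets would be reassuring but would not rule out a small effect.

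Where the survey can still be changed, TANDI could be added to the separation rule in the panel samples. With four units, 12 of 24 orders remain, and TANDI would sit beside PedsQL or CHU9D more often. In the hospital survey the same change leaves 12 of 120 five-form orders and fixes the EQ-type forms at positions 1, 3 and 5 (144 of 720 orders with six forms). That weakens the randomisation meant to control order and fatigue, so the subset analysis is preferable there.
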